#### Workflow efficiency

Workflow efficiency is a primary outcome for the Aim 2 trial that will be assessed through two different measures. The first, referral processing, will be obtained by capturing the time from screening to referral via EHR (Epic) timestamps. The second, referral quality, will be based on provider reports of referral to appropriate service following depressions screening. Both measures will be collected at the 6-month timepoint following completion of the Aim 2 trial.

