### Implementation gaps in depression screening

Effective implementation requires a team of individuals across the cascade to communicate and coordinate in a clear and timely manner. Although system-wide interventions such as universal screening policies and mutual access to EHRs between provider specialties can be facilitative, implementation gaps remain in the depression treatment cascade [11]. For example, not all children are screened, and for those who are screened, timely follow-up and linkage to care in response to elevated scores does not consistently occur. More recent and detailed local data [7] support these implementation gaps. All adolescents screened at risk for moderate-severe depression receive a list of behavioral health self-referral options including internal and external services. However, only internal behavioral health referrals are tracked uniformly at Rady Children’s Health Network.

This project proposes that intra-organizational alignment can serve as a mechanism potentially mediating the association of organizational context (e.g., implementation climate) with implementation outcomes [12–14] (e.g., acceptability, appropriateness) to mitigate gaps in the referral to treatment cascade. This approach is consistent with recent developments in organizational research that consider implementation climate and climate strength, a measure of alignment within groups [15]. However, this study will consider intra-organizational alignment across organizational levels. Integrating team effectiveness approaches with implementation science, such as through coordinated specialty care or collaborative care models, is a promising solution to address gaps related to continuous provider communication and coordinated decision-making about evidence-based depression screening, assessment, and service engagement [16–18].

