#### Clinical outcomes

Clinical outcome measures will include responses to elevated depression score and time (in days) to service linkage from elevated PHQ score. This will be measured with data from the EHR at baseline, 3 months, and 6 months.

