### Data management

#### Analytic plan

For Aims 2 and 3, we will use multilevel modeling with random intercepts and slopes to test the preliminary effects of TCT on implementation and service outcomes (Aim 2) and mechanisms (Aim 3). Refer to Table 2 for measures of outcomes and mechanisms. Specifically, outcomes include team member-reported acceptability, appropriateness, feasibility and workflow efficiency, and child service outcomes. Potential mechanisms are the proposed mediators of implementation climate, psychological safety climate, communication/coordination, and shared cognitions (see Table 2). Clinic will be included as a covariate (fixed effect). To test the effects of TCT a Group [current implementation vs. TCT] X Time [Baseline, 3, 6 Months] cross-level interaction will be assessed for each outcome. If a statistically significant (*p* < .05) interaction term is evident, simple slopes analyses will be conducted.

Quantitative data and qualitative data will be first analyzed separately. First, quantitative analyses of mechanisms of the TCT implementation strategy will be analyzed using the analytic approach described in Aim 2. To examine the hypothesized mediated effects of implementation strategy condition on implementation and service outcomes, multilevel path analysis will be conducted. Measures of Implementation Climate, Intra-Organizational Alignment, Communication and Coordination, Shared Cognitions, and Psych Safety will be tested as mediators in respective models. The specific mediated effects within these models will be tested using the bias-corrected bootstrap approach [38]. Qualitative interview data will be analyzed using rapid qualitative methods [28] based on a templated summary, deductive approach focused on specified team mechanisms. Specifically, the research team will code transcripts for changes in proposed mechanisms as explanatory factors in implementation and service outcomes. We will then use a mixed-methods analytic approach to synthesize the qualitative and quantitative data collected to examine convergence (i.e., do the two methods confirm or find similar results), complementarity (i.e., do the two methods provide more depth of understanding of research questions), and expansion (i.e., do the two methods provide insights beyond either method alone).

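### Days to referral and days to linkage exist only for youths who reach the event, and the single multilevel model says nothing about the rest, so the TCT effect can be understated or, under a condition, reversed

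*Protocol article*

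**What the plan says.** Two outcomes are durations.

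- **Time to referral.** Under Workflow efficiency, the article states that "Workflow efficiency is a primary outcome for the Aim 2 trial". The first of its two measures, referral processing, "will be obtained by capturing the time from screening to referral via EHR (Epic) timestamps". It is collected at 6 months.
- **Time to linkage.** Under Clinical outcomes, the article lists "time (in days) to service linkage from elevated PHQ score", taken from the EHR at baseline, 3 months and 6 months. It is not labelled primary.

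On analysis, the Analytic plan says "we will use multilevel modeling with random intercepts and slopes to test the preliminary effects of TCT on implementation and service outcomes", and that a Group-by-Time "cross-level interaction will be assessed for each outcome". No time-to-event method, censoring rule or value for a youth without an event is named.

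On how often the event fails to occur, the section on implementation gaps says that "timely follow-up and linkage to care in response to elevated scores does not consistently occur" and that "only internal behavioral health referrals are tracked uniformly". It gives no proportion for either. Occurrence is measured separately, through the response to an elevated score (Clinical outcomes) and through caregiver- or patient-reported linkage inside or outside the network at 3 and 6 months (Mental health service linkage).

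**The concern.** A youth with no referral or linkage date has no duration to enter into the stated model. Unless a rule is added, the analysis set for these outcomes is the youths who reached the event. Youths whose elevated score falls shortly before the data are extracted add to the problem, because their event may simply not have happened yet.

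Whether a youth is referred or linked is settled after randomisation and is what TCT is meant to change. Restricting to those reached therefore compares different kinds of youth in the two arms. If TCT brings in youths who would otherwise have been missed, they enter the TCT average and have no counterpart in the control average. The mean can then hide a real gain or, if these youths are slow, show a loss. The Discussion says the pilot will supply preliminary data for a definitive test, so a diluted or wrong-signed estimate could mislead that next step.

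**Working it through.** **Inputs.** The article gives no referral rate, linkage rate or time distribution, so it has no figure on this point to reproduce. Its only design figure, the 80% power for 20 clinicians per arm, does not bear on this question. All rates and times below are assumptions. *Reached* means referred or linked.

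**Illustration 1: fixed times, 30-day window, 100 youths with an elevated score per arm.** Control reaches 50 at a mean of 3 days. TCT reaches the same 50 at 2 days and a further 20 at a mean of x days. Youths not reached count as 30 days in the all-youth mean.

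- Control, mean among reached: 3.0 days.
- Control, all-youth mean: (50×3 + 50×30)/100 = 16.5 days.
- TCT, mean among reached: (50×2 + 20x)/70.
- TCT, all-youth mean: (50×2 + 20x + 30×30)/100.

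| x (days) | TCT, among reached (control 3.0) | TCT, all youths (control 16.5) | Reading among reached |
|---|---|---|---|
| 2 | 140/70 = 2.0 | 1040/100 = 10.4 | right direction |
| 4 | 180/70 = 2.6 | 1080/100 = 10.8 | right direction, small |
| 5.5 | 210/70 = 3.0 | 1110/100 = 11.1 | no effect |
| 12 | 340/70 = 4.9 | 1240/100 = 12.4 | TCT looks worse |

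Break-even with 20 added youths: (100 + 20x)/70 = 3 gives x = 5.5 days. With 10 added youths: (100 + 10x)/60 = 3 gives x = 8 days. At 10 to 14 days, those 10 give 200/60 = 3.3 to 240/60 = 4.0 days.

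**Illustration 2: other assumed times.** Control reaches 50% at a mean of 10 days. TCT leaves them at 10 days and adds 20% at 20 days: (50×10 + 20×20)/70 = 12.9 days, worse than 10. If TCT also speeds the first group by 20%: (50×8 + 20×20)/70 = 11.4, still worse. If the added youths take 10 days and the others are unchanged, the mean is (500 + 200)/70 = 10.0; at 5 days it is (500 + 100)/70 = 8.6. Neither is a reversal.

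**Illustration 3: proportional hazards.** Assume exponential times, follow-up T = 180 days, 50% reached in control and a hazard ratio of 2.

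- Mean among reached = 1/λ − T·e^(−λT)/(1 − e^(−λT)).
- Restricted mean over all youths = (1 − e^(−λT))/λ.
- Control: 1/λ = 180/ln 2 = 259.7. Among reached, 259.7 − 180×0.5/0.5 = 79.7 days; restricted mean 0.5×259.7 = 129.8 days.
- TCT: 1/λ = 129.8 and 75% are reached. Among reached, 129.8 − 180×0.25/0.75 = 69.8 days; restricted mean 0.75×129.8 = 97.4 days.

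The difference is 79.7 − 69.8 = 9.9 days (12%) among those reached, against 129.8 − 97.4 = 32.4 days (25%) over all youths. The direction is right and the effect is understated.

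**The case against.** The strongest reply is that the article says less than a critic might read into it. Five points deserve a fair answer.

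- **A linear model that drops youths without an event.** A reader might infer this, but neither word is in the text. A multilevel model can have another link, and a full protocol or SAP may set a rule. This stands as a limit. Even so, the article commits one model to each outcome, and an undefined duration cannot enter it as a value.
- **Many youths go unreferred, so the primary outcome is badly hit.** The documents do not show this. The statement on inconsistent follow-up concerns timely follow-up and linkage, and the description of the clinical intervention says that patients in the stated PHQ-9 range without elevated suicide risk are referred. The evidence for non-events is direct for linkage and weaker for referral, and linkage time is not called primary.
- **TCT will look worse because it reaches more youths.** This does not follow. Reversal needs the added youths to be slow enough; Illustration 3 and the faster cases show no reversal.
- **A slope per youth over three waves cannot be fitted.** This is not established. Referral processing is collected at 6 months only, and the article does not say that the youth is the unit of the slope.
- **Failures are measured elsewhere.** Response to an elevated score, referral quality and reported linkage could each show that more youths were reached. That lowers the risk of a wrong overall conclusion but does not repair the duration outcomes, which could still point the other way.

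**Conclusion.** The point holds in a limited form. Time to linkage and, on thinner evidence, time to referral are defined only for youths who reach the event, and the stated analysis does not deal with the others. An analysis confined to those reached selects on something TCT is meant to alter. It can understate the effect (9.9 days against 32.4 in the proportional-hazards illustration). It can reverse it when the added youths are slow (3.0 to 4.9 days among reached while the all-youth mean falls from 16.5 to 12.4).

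These sizes rest wholly on assumed rates and times. They show what can happen, not what is expected here. For a four-clinic pilot testing preliminary effects, with occurrence measured separately, this should be fixed; it does not invalidate the trial.

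**What to change.** State the following for both duration outcomes.

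1. **Denominator:** every youth with an elevated PHQ score, assigned to the period in which that score occurred.
2. **Analysis:** either time to event with censoring at the end of follow-up, summarised if wished by restricted mean time, or the proportion referred and the proportion linked within a fixed window (30 days is used above only as an example). Respect clustering by clinic; with two clinics per arm, also show each clinic's result.
3. **Extract:** if the fixed window is chosen, run the EHR extract on by that window after the last counted score. With censoring this is not required.
4. **Linkage event:** because "only internal behavioral health referrals are tracked uniformly", define the EHR event as internal linkage. Read it beside the caregiver- or patient-reported internal and external linkage, so that youths linked outside the network are not counted as failures.
5. **Mean days among those reached:** descriptive only, shown with the number reached and the denominator.

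The cost is a change to the analysis wording, some added analysis of EHR data already planned for abstraction and, under the fixed-window option, a later extract (about one month for a 30-day window).

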### Participants

Participants from Aim 1 will be recruited from the outpatient ambulatory departments with the highest rates of depression screening and/or behavioral health referrals based on the most recent patient reports from the EHR. These participants will include clinic leaders who oversee clinical operations including depression screening, clinicians and bedside staff who initiate depression screening such as physicians, nurses, and medical assistants, as well as clinicians who manage triage and referral to behavioral health services including social workers, psychologists, and administrative staff (e.g., patient access representatives).

Participants for Aims 2 and 3 will include 40 clinicians or clinical staff (including physicians, nurses, medical assistants, and mental health providers) drawn from the 4 enrolled specialty care clinics (an average of 10 clinicians per clinic). The specialty care clinic structure comprises all relevant members of the care cascade including a clinician who initiates the depression screening, medical provider who support screening completion, a behavioral health provider who responds to both an elevated depression screen and triages to the patient access representatives who are expected to confirm linkage to a behavioral health provider. Based on data from FY 2023, both inpatient and outpatient specialty services have high rates of depression screening.

Although youth are not participants in this project, the focal pediatric population will be youth ages 12–17 years who have a service encounter in the past year. This age range was selected because it aligns with the age range of the current depression screening protocol at Rady Children’s Health Network [7]. De-identified youth patient data will be abstracted from the EHR to determine movement through the screening-to-treatment cascade and workflow efficiency (i.e., time to complete each step in the cascade and referral quality).

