### Measures

Multiple measures will be used to assess the outcomes of TCT for Aims 2 and 3. Please refer to Table 2 for a full list of study constructs, outcomes, and the corresponding measures.

**Table 2 Tab2:** Study Constructs and measures (Aims 2 and 3)

Construct		Purpose	Source	Measure	Timepoint
Implementation outcomes	Acceptability, Appropriateness, Feasibility	Outcome	Provider	-Acceptability of Intervention Measure -Intervention Appropriateness Measure -Feasibility of Intervention Measure; Qualitative Interviews	6 mos
	Workflow Efficiency	Outcome	EHR and Provider	-Time from screening to referral via EHR timestamps (referral processing) -Referral to appropriate service (referral quality)	
Team-Level mechanisms	Implementation Climate	Mechanism	Team	Jacobs et al. Implementation Climate Measure [33]	BL, 3 mos., 6 mos
	Intra-Organizational Alignment	Mechanism	Team	Alignment is assessed by the degree to which team members from different organizational levels (e.g., physician, nurse, medical assistant, social worker) exhibit similarity on Psychological Safety Climate and Implementation Climate measures	
Team member-level mechanisms	Communication and Coordination	Mechanisms	Team	Collaboration and Satisfaction About Care Decisions (CSACD)—Collaboration	
	Shared Cognitions	Mechanism	Team	Shared Mental Model via card sorting task	
	Psych Safety	Mechanism	Team	Edmondson’s Psychological Safety Climate	
	Team Indicators	Exploratory	Team	NLP data sources	Monthly; 6 mos
Clinical/service outcomes	Child demographics	Sample characteristics	EHR	Family Demographics Questionnaire	BL, 3 mos., 6 mos
	Clinical outcomes	Outcome	EHR	-Response to elevated depression score -Time (days) to service linkage from elevated depression score	BL, 3 mos., 6 mos
	*Mental Health **Service Linkage*	*Outcome*	*Caregiver*	*-Report of linkage to any mental health service (internal/Rady and external/outside of Rady) following elevated depression score*	*3 mos., 6 mos*
Setting factors	Medical clinic characteristics		EHR and Provider	-# providers -Average patient volume -Patient case-mix: child race/ethnicity, health insurance (public versus private), age	BL

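### Referral quality, one of two measures of a primary outcome, is given conflicting data sources, and the provider-report version is open to differential reporting and has no baseline

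*Protocol article*

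**What the plan says.** All references are to the Protocol article.

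- **Workflow efficiency section.** "Workflow efficiency is a primary outcome for the Aim 2 trial that will be assessed through two different measures". The first measure, referral processing, comes from "capturing the time from screening to referral via EHR (Epic) timestamps". The other, referral quality, "will be based on provider reports of referral to appropriate service following depressions screening". Both are collected at 6 months.
- **Participants section.** "De-identified youth patient data will be abstracted from the EHR" in order to determine, among other things, "workflow efficiency (i.e., time to complete each step in the cascade and referral quality". This places referral quality in the record.
- **Measures section, Table 2.** The workflow efficiency row has the source "EHR and Provider" and lists the measure as "Referral to appropriate service (referral quality". The source is given once for the row, not for each measure.
- **Analytic plan.** Workflow efficiency appears in the list of team member-reported outcomes. A Group x Time interaction over baseline, 3 and 6 months is to be assessed for each outcome.

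**The concern.** A primary outcome measure needs one stated source. Here a self-report and a record abstraction are both described for the same quantity. They can give different answers, and the choice between them should not remain open until data are seen.

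The choice also affects validity. The providers described as Aim 2 participants are 40 clinicians and staff of the four randomized clinics. Under Specific Aim 2, TCT staff attend two training sessions, receive biweekly feedback on their communication in the EHR and have booster coaching over six months. They cannot be unaware of that training. If they also supply the reports behind a primary outcome measure, the arms may differ in how staff report as well as in what happened to referrals.

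A report taken once, at 6 months, cannot separate a pre-existing difference between clinics or a reporting tendency from an effect of TCT. The pilot is meant to supply preliminary data for a definitive test (Discussion), so a distorted estimate would carry forward.

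**Working it through.** **1. Sources side by side**

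| Section | Source of referral quality |
|---|---|
| Workflow efficiency | Provider reports |
| Participants | De-identified EHR abstraction |
| Table 2 | EHR and provider, for the construct as a whole |
| Analytic plan | Team member-reported, for workflow efficiency as a whole |

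The first two rows conflict. Table 2 could fit either, or a split by measure. The Analytic plan does not fit the timestamp source of referral processing either.

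**2. Timing against the analysis**

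The measure is collected at one time point (6 months). The planned test is a Group x Time interaction over three time points. With one time point there is no change over time to compare, so the interaction cannot be estimated for this measure.

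**3. What a reporting difference could do**

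The plan gives no figure on this point, so there is none to reproduce. Both illustrations below rest on assumed inputs.

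*(a) Shift in SD units.* Inputs from the Power analysis section: 20 clinicians per arm and alpha 0.05. Assumed: no true effect, a two-mean z-test, clustering ignored, and a differential reporting shift of b SD.

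se = sqrt(2/20) = 0.316

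P(reject) = Phi(b/se - 1.96) + Phi(-b/se - 1.96)

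| b (SD) | P(reject) |
|---|---|
| 0 | 5.0% |
| 0.1 | 6.2% |
| 0.2 | 9.7% |
| 0.3 | 15.8% |
| 0.5 | 35.3% |

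For b = 0.2, b/se = 0.632 and Phi(-1.328) + Phi(-2.592) = 0.092 + 0.005 = 0.097. The formula is symmetric in b, so a shift against TCT gives the same probabilities.

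*(b) Shift in percentage points.* Assumed: 70% of referrals are truly appropriate in both arms, and staff in one arm report an extra 10% to 30% of the inappropriate ones as appropriate.

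0.30 x 0.10 = 0.03, and 0.30 x 0.30 = 0.09

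The spurious difference is 3 to 9 points. It favors TCT if the over-reporting is in the TCT arm and the comparison if it is there.

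**The case against.** **The sections might be compatible.** The Participants section does not say that the EHR is the only source, Table 2 names both, and a provider report could be documented in the EHR. That is possible, but the article does not say so. This is not detail left to a fuller document: the article does name the source, and names it differently in different places.

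**The bias is inferred.** A reader might infer that TCT clinicians grade their own referrals and will therefore favor TCT. The documents do not support that. They do not say who reports, on whose referrals, or who judges appropriateness. Awareness of TCT follows from the design and is not stated. Training could also make staff more critical. Comparison staff are given expectations about handoff, and TCT feedback concerns communication within the team, not referral appropriateness. What stands is a risk of unknown direction and size.

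**The EHR is not a clean alternative.** According to the section on implementation gaps, only internal behavioral health referrals are tracked uniformly. Staff who know their arm also make the EHR entries, and TCT feedback on EHR communication may change what is written down. Both points stand and belong in the fix.

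**The missing baseline is not special to provider report.** Referral processing is also set at 6 months only. That is correct. The difference is that the article already plans EHR abstraction of clinical outcomes at baseline, 3 and 6 months (Clinical outcomes section), whereas a provider report not collected at baseline cannot be recovered later.

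**Other outcomes do not rest on provider report.** Referral processing, time to linkage, and caregiver or patient report of linkage are independent of it. This limits the damage to the trial as a whole but does not settle the source of this measure.

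**Conclusion.** The point holds as a contradiction in the source of one primary outcome measure, with a measurement risk if the Workflow efficiency section is followed as written. That version would rest on reports apparently made by staff who know whether they received TCT. It would also supply no baseline for the analysis planned for each outcome.

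The size of any bias cannot be derived from the documents. The 9.7% to 35.3% and the 3 to 9 points show what assumed shifts would do and are not predictions for this trial.

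Two stronger readings should be avoided. Referral quality is not shown to be half of the primary outcome: the text says a primary outcome with two measures, and states no composite or weighting. Nor would an EHR rule remove all differential measurement. It removes self-report bias only.

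**What to change.** 1. Make the Participants, Measures (Table 2), Workflow efficiency and Analytic plan sections name the same source. In Table 2, give a source for each of the two measures.
2. Use the EHR abstraction already planned as the primary source. Define referral quality by one prespecified rule that compares the recorded referral or disposition with the health system's existing pathway, applied identically in both arms at baseline, 3 and 6 months. The article describes the referral step only for part of the PHQ range, so the rule must be taken from the full existing pathway. No new clinical rule is needed.
3. Keep provider report as a secondary measure, and state who reports and on which referrals.
4. State the limits. Either restrict the EHR measure to internal behavioral health referrals, or supplement it for external ones, for example with the caregiver or patient linkage report already planned at 3 and 6 months. That report has no baseline, so it can support the measure but cannot complete it. Say also that TCT may alter documentation.

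The cost is a written rule and a further query within the planned abstraction, plus handling of external referrals if they are included. A fixed rule also loses some clinical nuance, which is a reason to retain provider report as secondary.
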